## Abstract

**Background:**

About 2000 children and adolescents under the age of 18 are diagnosed with cancer each year in Germany. Because of current medical treatment methods, a high survival rate can be reached for many types of the disease. Nevertheless, patients face a number of long-term effects related to the treatment. As a result, physical and psychological consequences have increasingly become the focus of research in recent years. Social dimensions of health have received little attention in health services research in oncology so far. Yet, there are no robust results that allow an estimation of whether and to what extent the disease and treatment impair the participation of children and adolescents and which factors mediate this effect. Social participation is of great importance especially because interactions with peers and experiences in different areas of life are essential for the development of children and adolescents.

**Methods:**

Data are collected in a longitudinal, prospective, observational multicenter study. For this purpose, all patients and their parents who are being treated for cancer in one of the participating clinics throughout Germany will be interviewed within the first month after diagnosis (t1), after completion of intensive treatment (t2) and half a year after the end of intensive treatment (t3) using standardized questionnaires. Analysis will be done by descriptive and multivariate methods.

**Discussion:**

The results can be used to identify children and adolescents in high-risk situations at an early stage in order to be able to initiate interventions tailored to the needs. Such tailored interventions will finally reduce the risk of impairments in the participation of children and adolescents and increase quality of life.

**Trial registration:**

ClinicalTrials.gov: NCT04101123.

## Background

In Germany, approximately 2000 children and adolescents under the age of 18 are diagnosed with cancer each year [1]. Leukemias are the most common malignancies in children and adolescents, accounting for approximately 33% of all cancers, followed by brain tumors (25%). Other common malignancies in childhood are soft tissue sarcomas (6%) and bone tumors (5%) [1, 2]. Because of more differentiated diagnostics and standardized treatment protocols, survival rates have increased significantly in the last several decades [3]. Across all cancers, the 5-year survival rate is 85%. The probability of living more than 10 years after diagnosis is only slightly below this value [4]. The prognosis of brain tumors and sarcomas is worse than that of leukemias and highly depends on localization, tumor size, pathology, and possibilities of tumor removal [2].

Due to this success of treatment, cancer in childhood has changed from an acute life-threatening to a curable illness. However, the price for this cure often lies in a not inconsiderable rate of long-term consequences to which not much is known yet. Thus, late effects addressed by patients have gained attention in pediatric oncology research. In addition to the consequences of chemotherapy and radiation (e.g., fatigue, emotional distress), other effects may develop later, such as fertility disorders, metabolic disorders, secondary malignant tumors, cognitive impairments, and cardiac problems [5–7]. Some of these conditions even develop years after the end of treatment. Even young adults who have been treated for cancer in childhood still report neurocognitive impairments and reduced vitality and suffer from sleep disturbances and fatigue [8]. These issues require an adaption of one’s lifestyle, for example, a reduced workload with respect to school, work, or even leisure activities [9, 10]. The effects for children and adolescents are particularly serious, as they undergo important developmental phases during cancer treatment. Children’s ability to participate in social activities can be considerably limited [11]. However, interacting with peers is a fundamental component of children’s and adolescents’ development of social skills and competencies [12]. To avoid disadvantages in psychosocial development, it is important to quickly reintegrate children and adolescents with cancer into social life. There are already a number of studies that focus on the impact of childhood cancer on quality of life [13, 14]. Social dimensions of health, such as activity and participation, have rarely been investigated in pediatric oncology. Here, activity means the concrete execution of an action and participation the involvement in life situations. To date, no reliable results, neither international findings nor those for Germany, are available for use in estimating whether and to what extent the disease and treatment are associated with restrictions in social participation and the factors that mediate this effect. Furthermore, it is unclear to what extent social inequalities contribute to better or worse disease management by influencing personal and social factors.

### Study objectives

The aim of the study is to investigate the influence of social determinants, particularly the socioeconomic position of the parents, on participation and activity in children and adolescents between 10 and 18 years with leukemia, brain tumors and sarcomas. Furthermore, personal and treatment-related factors and their effects on participation will be explored.

Our study hypotheses are as follows (Fig. 1):
Participation and activities in children and adolescents with leukemia, brain tumors and sarcomas vary during and after cancer treatment in relation to the socioeconomic position of the parents.Personal, social, and treatment-related factors are associated with the participation and activity of children and adolescents with leukemia, brain tumors and sarcomas during and after cancer treatment.The socioeconomic position of the parents influences personal, social, and treatment-related factors of children and adolescents with leukemia, brain tumors and sarcomas during and after cancer treatment and may therefore explain the findings for participation and activity.Personal, social, and treatment-related factors as well as participation and activity are related to quality of life in children and adolescents with leukemia, brain tumors and sarcomas during different phases of cancer therapy and after treatment.Predictors can be identified from personal, social, and treatment-related factors that can already be used to estimate a risk of low participation during cancer treatment.

**Fig. 1 Fig1:**
[figure not shown]
Study hypotheses

Primary endpoints are social participation, activity, and quality of life. Secondary endpoints are illness perceptions, self-concept, self-efficacy, sense of coherence, social support, coping, optimism, psychosocial problems and strengths, mental health, fatigue, psychosocial needs and evaluation of the treatment.

## Methods/design

The study protocol complies with the STROBE guidelines for the reporting of observational studies.

### Study design

The SUPATEEN study is designed as a multicenter, longitudinal, prospective, observational study in Germany. The patients and one of their parents will be interviewed during the first month after diagnosis (t1), at the end of intensive treatment (t2), and half a year after end of intensive treatment (t3). At t1, paper-based data collection is conducted in the hospital. At t2 and t3, participants will have the choice to receive the questionnaire via mail or complete it online. The equivalence of written and electronic data collection is well-documented [15]. For the internet-based survey, the software CHES (Computer-Based Health Evaluation System) will be used. The software has already proven itself in practice and is supported by the European Organisation for Research and Treatment of Cancer (EORTC) [16].

### Eligibility

Patients aged 10–18 years of both sexes who are newly diagnosed with confirmed leukemia, brain tumors or sarcomas of all stages of cancer are eligible for this study. They must be admitted for the treatment of their disease in one of the participating study centers. Additionally, we include one parent of each patient. Parents must give written consent for the participation of their children if they are under the age of 18. The exclusion criteria are as follows: a) having a relapse or secondary tumor, b) insufficient command of German, c) profound cognitive and physical impairments, and d) no written informed consent.

### Recruitment

Any patient meeting the inclusion criteria will be informed about the study within the first month after diagnosis by the responsible clinic staff at the study center. After explaining the content and objectives of the study as well as the voluntary nature of participation and adherence to the protection of data of children and adolescents and their parents, the clinic staff will distribute the questionnaires. Completed questionnaires are returned to the clinic staff in a sealed envelope. Patient enrollment will last for 18 months. Reminders, questionnaires, and login details for follow-ups will be sent from the study center in Halle. In cases of refusal, patients are asked to provide the following information: their age, gender, disease type and reasons for declining participation for responder analyses.

### Sample size

The inclusion of many study centers and a large study population (encompassing patients with the three most common cancers in childhood and adolescence) facilitate the recruitment of an adequately sized sample. The participating clinics treat approximately 470 children and adolescents between the ages of 10 to 18 years with leukemia, brain tumors, and sarcomas per year. With a recruitment time of one and a half years, approximately 700 patients are eligible for the study. A conservatively estimated response rate of 70% [17] and a further 30% loss to follow-up [18] will leave approximately 340 complete cases. With this sample size, we can test our hypotheses and include a total of 30 independent variables and confounders [19].

### Instruments

Data collected during each survey time point are detailed below and in the Table 1.

**Table 1 Tab1:** Measures and time points for patients and parents

Outcomes	Instruments	t1		t2		t3	
		Patient	Parent	Patient	Parent	Patient	Parent
Demographics	Standard inventory	x	x				
Clinical data	CRF	x		x		x	
Participation	CASP	x		x		x	
Evaluation of the treatment	FBB			x	x		
Self-concept	SDQ	x		x		x	
Fatigue	EORTC QLQ-C30	x		x		x	
Social Support	SSS	x		x		x	
Illness perception	IPQ	x		x		x	
Self-efficacy	SWE	x		x		x	
Optimism	BFW	x		x		x	
Autonomy	Kidscreen	x		x		x	
Psychosocial problems/strengths	SDQ-D	x		x		x	
Familial burden	FaBel				x		x
Family resources	FES		x				x
Psychosocial needs	SCNS-SF-34		x		x		
Satisfaction with life	SWLS		x		x		x
Doctor-parent relationship	PRA-D				x		
Quality of life	KINDL-R	x		x		x	
	SF-12		x		x		x
Sense of coherence	C-SOC	x		x		x	
	SOC-L9		x		x		x
Coping	CODI	x		x		x	
	CHIP-D		x		x		x
Mental health	ChilD-S	x		x		x	
	HADS		x		x		x

#### Sociodemographic and clinical data

Sociodemographic characteristics will be assessed via self-report with a standardized inventory. Clinical data will be ascertained from the medical records and include information about ICD-10 diagnosis, disease stage, current treatment, and comorbid conditions.

#### Social participation and activity

To evaluate social participation and activity, we will use the Child and Adolescent Scale of Participation (CASP) [20, 21]. This self-report questionnaire measures the extent to which children and adolescents participate in home, school, and community activities in comparison to their peers. The instrument consists of 20 items that form 4 subscales (home participation, school participation, community participation, home and community living activities).

#### Evaluation of the treatment

The Questionnaires of the Evaluation of Treatment (FBB) evaluate the therapy and quality of treatment from the children’s and parents’ perspectives [22]. The children’s and parents’ version consists of 20 items that can be summarized in a total score or scores on 3 subscales (success of the treatment, relationship to medical team, treatment conditions).

#### Self-concept

To assess self-concept, we use 3 dimensions (physical appearance, parent relations, peers) from the short version of the Self-Description Questionnaire (SDQ) [23, 24]. The questionnaire measures the self-concept of children in different domains via self-report. Every subscale consists of 3 items.

#### Fatigue

We will use the fatigue scale from the European Organization for Research and Treatment of Cancer Quality of Life Questionnaire (EORTC QLQ-C30) [25] to ascertain patients’fatigue symptoms.

#### Social support

Social support will be measured with the Social Support Scale (SSS) [26, 27]. The 8-item self-report instrument assesses support in terms of showing affection, listening, providing information, and engaging in activities together via self-report.

#### Illness perception

The revised version of the Illness Perception Questionnaire (IPQ-R) measures individual beliefs and feelings about an illness and is based on Leventhal’s self-regulatory model [28]. We will use the following 3 scales: personal control, treatment control, and coherence.

#### Self-efficacy

The generalized self-efficacy scale (GSE) consists of 10 items and assesses self-beliefs about coping with difficult demands in life (perceived self-efficacy) [29].

#### Optimism

We will use the 8-item scale of a positive attitude toward life from the Bern Subjective Well-Being Questionnaire for Adolescents (BFW) to evaluate optimism [30]. This scale ascertains a generally positive attitude (“see the good side”) as well as one’s personal conviction to lead a good life.

#### Autonomy

To evaluate children’s and adolescents’ autonomy, the 5-item autonomy scale from the Kidscreen questionnaire will be used [31]. This scale measures the opportunities to create social and leisure time and will be summarized in a total score.

#### Psychosocial problems and strengths

To assess psychosocial problems and strengths, we will use the Strengths and Difficulties Questionnaire (SDQ) for the self-report of children and adolescents [32]. The instrument consists of 25 items equally divided across 5 scales (emotional problems, conduct problems, peer problems, hyperactivity, and prosocial behavior).

#### Familial burden

Familial burden will be ascertained with the short form of the Impact on Family Scale (FaBel-11) [33]. The items are summarized in a total score and include questions about the general negative impact of parents, social relationships, and financial burden.

#### Family resources

A shortened version of the German adaption of the Family Environment Scale (FES) will be used to assess family resources [34, 35]. The instrument contains 12 items that form 3 subscales (cohesion, control, family activities) and a total score.

#### Psychosocial needs

To evaluate the psychosocial needs of the parents, the short form of the Supportive Care Needs Survey (SCNS-SF-34-D) will be used [36]. In this 34-item questionnaire, unmet needs will be reported in 5 domains (physical and daily living needs, psychological needs, patient care and support needs, health system and information needs, sexuality needs). For this study, the sexuality scale was omitted.

#### Satisfaction with life

The Satisfaction With Life scale is a 5-item instrument that measures global life satisfaction and subjective well-being [37]. Answers will be summarized in a total score.

#### Doctor-parent relationship

The quality of the doctor-parent relationship will be assessed with the Patient Reactions Assessment (PRA-D) [38, 39]. The instrument contains 15 items that are equally divided across 3 scales (information, affectivity, communication).

#### Quality of life

The KINDL questionnaire will be used to ascertain children’s and adolescents’ health-related quality of life [40]. Parents’ quality of life will be assessed with the 12-item Short Form Health Survey (SF-12) [41]. The instrument can be summarized in a total score for physical and mental health.

#### Sense of coherence

To assess sense of coherence in children and adolescents, the Children’s Sense of Coherence Scale (C-SOC) was used [42]. The instrument contains 12 items about children’s sense of comprehensibility, manageability, and meaningfulness, which will be summarized in a total score. Parent’s sense of coherence will be measured with a short form of Antonovsky’s Sense of Coherence Scale (SOC-L9) [43].

#### Coping

The coping strategies of children and adolescents were evaluated using the Coping with a Disease (CODI) questionnaire [44]. The 28 items of the instrument form 6 scales (acceptance, avoidance, cognitive-palliative, distance, emotional reaction, wishful thinking) and an overall rating of the disease management. The coping skills of parents will be assessed with the Coping Health Inventory for Parents (CHIP-D) [45]. This questionnaire measures parental coping with chronic childhood disease with 45 items that form 3 scales (maintaining family integration, maintaining social support, understanding health care situation).

#### Mental health

The Children’s Depression Screener (ChilD-S) will be used to assess depressive symptoms in children and adolescents [46]. The 8 items of the instrument are summarized in a total score. Parental mental health will be evaluated with the Hospital Anxiety and Depression Scale (HADS), which contains 14 items (7 per scale: anxiety, depression) [47].

### Statistical analysis

All collected data will be checked for consistency, validity, and missing values. Descriptive statistics will be calculated for all study variables, and their correlations will be explored. Therefore, the strength of the association between the different independent variables and participation can be examined. Differences in social participation and activity, depending on the socioeconomic position of the parents, will be conducted using multiple linear regression and variance analyses. Both will be controlled for confounders such as age, sex, stage of disease, disease site, and treatment-related factors. In addition, multiple regression analysis will also be applied to identify which personal, social, and treatment-related factors are associated with participation and activity and whether the socioeconomic position of the parents is associated with these intermediate factors. Depending on the frequency and type of missing data, listwise deletion of patients with missing data or appropriate imputation techniques will be applied.

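### Treatment-related factors are adjusted for as confounders in the socioeconomic model although Hypothesis 3 treats them as intermediates, so Hypothesis 1 is not tested on the total socioeconomic difference

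*Protocol article*

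**What the plan says.** All references are to the protocol article.

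- **Aim (Study objectives, opening sentence):** "The aim of the study is to investigate the influence of social determinants, particularly the socioeconomic position of the parents, on participation and activity". Hypothesis 1 is that participation and activity vary with parental SEP.
- **Hypothesis 2 (Study objectives):** "Personal, social, and treatment-related factors are associated with the participation and activity of children and adolescents".
- **Hypothesis 3 (Study objectives):** "The socioeconomic position of the parents influences personal, social, and treatment-related factors of children and adolescents", and this "may therefore explain the findings for participation and activity".
- **Model for Hypothesis 1 (Statistical analysis):** "Differences in social participation and activity, depending on the socioeconomic position of the parents, will be conducted using multiple linear regression and variance analyses". The adjustment set follows at once: "Both will be controlled for confounders such as age, sex, stage of disease, disease site, and treatment-related factors".
- **Next sentence (Statistical analysis):** multiple regression will relate personal, social and treatment-related factors to participation, and will examine "whether the socioeconomic position of the parents is associated with these intermediate factors".

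The Discussion repeats that intermediary factors are to be used to explain inequalities in participation. The article describes no SEP regression without treatment-related factors. It does not divide them into a confounder subset and an intermediate subset.

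**The concern.** A confounder of the SEP-participation relation must not be a consequence of SEP. An intermediate is exactly that. Hypotheses 2 and 3 together set out a chain from SEP through treatment-related factors to participation, while the Hypothesis 1 model conditions on the middle link of that chain.

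Two things are at stake:

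- The coefficient reported for the study's leading question would be the part of the SEP difference that does not run through treatment-related factors. Hypothesis 1 asks about the whole difference.
- Hypothesis 3 asks how far intermediates explain the SEP difference. That requires a comparable regression coefficient before the intermediates enter, and the stated plan does not provide one.

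Conditioning on an intermediate can also introduce bias if treatment-related factors and participation share unmeasured causes.

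**Working it through.** **1. The two roles side by side**

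| Place | Role of treatment-related factors |
|---|---|
| Statistical analysis, adjustment sentence | confounders of the SEP comparison |
| Statistical analysis, next sentence | intermediate factors that SEP may be associated with |
| Study objectives, Hypothesis 3 | influenced by SEP, possible explanation of the participation findings |
| Study objectives, Hypothesis 2 | associated with participation and activity |

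The last three rows describe a mediator. The first is incompatible with them.

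**2. The plan's own figure**

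Sample size gives about 470 patients a year for 1.5 years, 70% response and 30% loss to follow-up. 470 × 1.5 = 705, stated as about 700, and 700 × 0.70 × 0.70 = 343. The stated figure of about 340 complete cases is reproduced. It is used below only as n. The article gives no effect size, alpha or power.

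**3. What adjustment does**

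Let a be the standardised path from SEP to a treatment-related factor, and b the path from that factor to participation. In a linear model:

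- total effect = direct effect + a × b
- SEP coefficient adjusted for the factor = total − a × b

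Assumptions: total effect 0.20; a and b as in the table; no unmeasured common cause of factor and outcome; two-sided alpha 0.05. Power is approximated as Φ(r√n / √(1 − r²) − 1.96) plus the small opposite tail, with n = 340 and r the coefficient.

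| a | b | a × b | Adjusted coefficient | Change from 0.20 | Approximate power |
|---|---|---|---|---|---|
| 0 | any | 0 | 0.20 | none | 96% |
| 0.1 | 0.1 | 0.01 | 0.19 | −5% | not computed |
| 0.2 | 0.2 | 0.04 | 0.16 | −20% | 85% |
| 0.3 | 0.3 | 0.09 | 0.11 | −45% | 53% |
| 0.4 | 0.4 | 0.16 | 0.04 | −80% | 11% |
| 0.3 | −0.3 | −0.09 | 0.29 | +45% | not computed |

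Example: for r = 0.16, 0.16 × √340 / √(1 − 0.0256) = 2.99, and Φ(2.99 − 1.96) = 0.85.

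The power column compares the chance of detecting two different quantities, the total and the direct effect. It shows what the choice of model could mean for the Hypothesis 1 test. It does not measure a loss of efficiency for one target.

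**4. With a shared unmeasured cause**

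Let an unmeasured variable affect the factor with path u1 and participation with path u2. The adjusted SEP coefficient becomes direct effect − a × u1 × u2 / (1 − a²). A simulation of 1,000,000 records agreed:

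- a = b = 0.3, direct 0.11, u1 = u2 = 0.5: 0.11 − 0.3 × 0.25 / 0.91 = 0.03 (simulated 0.027; total 0.198).
- a = 0.3, b = 0.1, direct 0.17, u1 = 0.5, u2 = −0.5: 0.17 + 0.3 × 0.25 / 0.91 = 0.25 (simulated 0.250; total 0.197).

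The shift can therefore go either way.

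**The case against.** **The term is undefined and the list is open.** Clinical data include current treatment, while the evaluation of treatment and the doctor-parent relationship are perceived aspects of care. The two uses of the phrase might cover different variables, the list is introduced as examples, and a full protocol or analysis plan may stage the models. This is possible, but the article uses one term for both roles in adjacent sentences and makes no distinction. The contradiction on the page stands.

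**Hypothesis 3 is a hypothesis.** It proposes that SEP influences these factors; it does not define them as consequences of SEP. That is correct. Even so, a plan that tests mediation should not condition on the proposed mediator in the model for the total difference.

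**A reader might infer that the SEP effect is biased toward zero.** The documents do not support this as a fact. They give no sign or size for any path, and the working shows shifts in both directions, and no shift when a = 0.

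**A reader might infer that nothing is left for Hypothesis 3 to explain.** This goes too far. The analysis section also plans descriptive statistics and correlations, so a crude SEP association will be available. What is missing is a stated regression for the total difference, adjusted for age, sex and disease.

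**Time order alone does not settle the adjustment set.** Disease site also arises after parental SEP is established, yet the article does not propose that SEP influences it. The argument here rests on Hypothesis 3, not on timing. The article likewise says nothing of whether SEP affects stage, so its role is a point to state and is not itself an error.

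**Conclusion.** Wrong as written. The article assigns treatment-related factors two incompatible roles, and the Hypothesis 1 model that results does not estimate the total SEP difference. This rests on the text alone.

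Direction and size are conditional. If Hypothesis 3 holds, the two paths work in the same direction as the total effect, and the relation between treatment-related factors and participation is unconfounded, the model would be expected to understate the difference. Under the assumed total of 0.20, the understatement runs from 5% (a = b = 0.1) to 80% (a = b = 0.4). Outside those conditions the coefficient may be larger than the total or unchanged. All path values are assumptions, so the range shows sensitivity and does not predict this study's result.

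**What to change.** - Remove treatment-related factors from the Hypothesis 1 adjustment set. Fit a primary SEP model adjusted for age, sex and disease site.
- State whether stage is treated as a confounder or as an intermediate, with the reason.
- Enter treatment-related factors, with the personal and social factors, only in a second model labelled as explanatory for Hypothesis 3. Report the SEP coefficient from both models.
- Interpret the change between the two coefficients as mediation only under a stated assumption of no unmeasured mediator-outcome confounding.

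The cost is a short rewording of the analysis section, one extra model, and possibly slightly larger residual variance in the primary model. No new data are needed. Trial status says enrolment has not begun, so the change can be made before any results are seen.

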## Discussion

For the first time, the study provides detailed results on the influence of social determinants on the social participation and activity of children and adolescents with leukemia, brain tumors, and sarcomas in Germany. Since these represent the three most common cancers in childhood and adolescents (> 60% of all new cases), meaningful insights can be gained for a large group of patients. Children and adolescents with impairments in social participation and quality of life can have health and emotional problems that should be recognized early. In addition, age-appropriate development can be hindered by limited interactions with peers. Thus, it is necessary to identify children and adolescents at risk of impaired social participation early in the course of treatment so that appropriate interventions can be initiated. In addition to the identification of risk groups, intermediary influencing factors are identified that can be used to explain inequalities in participation and activities.

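### The two association regressions stated for the third hypothesis do not estimate mediation, so they cannot support the claim that intermediary factors explain social inequality in participation

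*Protocol article*

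**What the plan says.** Under Study objectives, the third hypothesis holds that parental SEP influences personal, social and treatment-related factors and "may therefore explain the findings for participation and activity". That is a mediation hypothesis, worded with some caution. The Discussion is not cautious: "intermediary influencing factors are identified that can be used to explain inequalities in participation and activities".

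The Statistical analysis section names three pieces of work that bear on this:

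- SEP and participation: linear regression and variance analyses, adjusted for confounders.
- Factors and participation: multiple regression to find "which personal, social, and treatment-related factors are associated with participation and activity".
- SEP and factors: the same technique, to see "whether the socioeconomic position of the parents is associated with these intermediate factors".

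The section describes no model containing both SEP and the factors for this purpose, no comparison of the SEP coefficient with and without them, and no indirect effect. It also names no wave for factor or outcome. Table 1 shows CASP at t1, t2 and t3, together with most child-reported factors, including self-concept, fatigue, autonomy, psychosocial problems, coping and depressive symptoms. Demographics are collected at t1 only.

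**The concern.** Showing that SEP is associated with a factor, and that the factor is associated with participation, does not show that the factor carries any of the SEP difference. The same pair of associations appears when SEP affects participation by another route and participation then affects the factor.

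That reverse direction is plausible here. A child who is cut off from school and friends may become low in mood, report more peer problems and score lower on autonomy. The autonomy scale asks about opportunities for social and leisure time, which lies close to the outcome itself. All of these are the same child's self-reports, taken on the same occasions as CASP.

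What is at stake is the explanatory conclusion announced in the Discussion. A consequence of low participation could be presented as a reason for the social gradient.

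**Working it through.** **Inputs from the protocol article (Sample size).** About 470 patients per year, 1.5 years of recruitment, about 700 eligible, 70% response, 30% loss to follow-up, about 340 complete cases.

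**The plan's own figure.** 470 × 1.5 = 705, stated as about 700. Then 700 × 0.70 × 0.70 = 343, or 705 × 0.49 = 345. The stated 340 is reproduced.

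**Inputs not in the documents (assumptions).** Correlation a between SEP and participation: 0.1 to 0.3. Correlation c between participation and factor: 0.3 to 0.7. Slope of t3 on t1 participation: 0.6. Variables standardised, two-sided 5% tests, no further covariates.

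**Scenario.** Pure reverse causation: SEP affects participation, participation affects the factor, and the factor never affects participation. The factor explains nothing, so every declared explanation is false.

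**Hand check at a = 0.2, c = 0.5.**

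- The induced SEP–factor correlation is a × c = 0.10.
- With N = 340, t = 0.10 × √338 / √(1 − 0.01) = 1.85.
- The chance of exceeding 1.96 is about P(Z > 1.96 − 1.85) = 46%.
- The factor–participation regression, at correlation 0.5, is significant almost always. Both together are therefore significant in about 45% of studies.

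**Simulation (N = 340, 2,000 runs per setting).** Share of runs that declare the factor an explanation:

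| a | c | Both stated regressions significant (same wave) | Same-wave indirect effect (Sobel) | Time-ordered, adjusted for SEP and t1 participation |
|---|---|---|---|---|
| 0.1 | 0.3 | 8.8% | 6.5% | 0.6% |
| 0.2 | 0.3 | 19.5% | 16.1% | 1.4% |
| 0.2 | 0.5 | 45.3% | 43.9% | 2.8% |
| 0.3 | 0.5 | 78.7% | 77.6% | 4.2% |
| 0.3 | 0.7 | 97.5% | 97.5% | 4.6% |

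The fourth column shows that adding an indirect effect to same-wave data does not help. The time order, with adjustment for earlier participation, does the work. The last column requires both paths to be significant: SEP to t1 factor, and t1 factor to t3 participation.

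**Limits of the time-ordered model, same set-up with a = 0.2 to 0.3 and c = 0.5 to 0.7.**

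- The last column assumes that CASP is measured without error. At CASP reliability 0.8 the false rate is about 10% to 50%, and at 0.7 it reaches about 70%. The higher ends belong to c = 0.7.
- If mediation is genuine but already complete at t1, the model adjusted for t1 CASP finds it in only about 5% of runs at perfect reliability, because t1 CASP lies on the pathway.

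**The case against.** The strongest reply is that the article is silent on waves and does not choose same-wave models. The study is longitudinal and prospective, the confounder list is open-ended, and wave assignment, baseline adjustment and the choice of estimator may be settled in an analysis plan that is not shown. This stands in part. A reader might infer that the plan has decided to ignore time ordering, and the text does not support that. What remains is that the article itself states the method for the third hypothesis and the conclusion to be drawn from it, and the first does not deliver the second. An analysis plan that only elaborated the stated method would keep the mismatch.

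Three other stronger readings also fail:

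- **A fixed share falsely explained.** Adding a same-wave consequence to the SEP model would shrink the SEP coefficient. With a = 0.2 and c = 0.5 it falls to 0.2 × 0.75 / 0.99 = 0.152, an apparent 24% explained. The plan does not state that model, so this is not a forecast of its output.
- **Intervention targets.** The documents link interventions to early identification of children at risk, not to acting on the intermediary factors. Harm through wrongly chosen targets is an extrapolation.
- **The second hypothesis.** It concerns association only, and the stated regression fits it.

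It is also fair to say that reverse causation is less plausible for clinical data taken from records, and that the time-ordered model is no complete cure. Both points stand.

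**Conclusion.** The concern holds as a mismatch between stated method and stated claim. Two separate association regressions do not estimate the part of the SEP difference that passes through a factor. With no wave fixed, they could present a consequence of low participation as its explanation. It would go too far to say that this will happen.

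Under pure reverse causation at N = 340, the false rate is about 45% at assumed correlations of 0.2 and 0.5, and about 9% to 97% over the assumed range. These rates rest on correlations that the documents do not give and on same-wave use, which the documents leave open. The lack of an indirect effect depends on neither.

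Time ordering with t1 CASP adjustment lowers the false rate to about 5% or less if CASP is measured without error, and by less otherwise. The point should be settled before the analysis is fixed. The article reports that enrolment has not started.

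**What to change.** For the third hypothesis only, prespecify the following:

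- A model with SEP at t1, the factor at an earlier wave and CASP at a later wave, adjusted for t1 CASP. When the t2 factor is used, adjust for its t1 value where one exists.
- The indirect effect with a bootstrap confidence interval.
- A sensitivity analysis without the t1 CASP adjustment. The main analysis targets change after t1, while the sensitivity analysis also admits mediation already present at t1, at the price of readmitting reverse causation.
- FaBel, PRA-D and FBB used only as factors for CASP at t3, because Table 1 first collects them at t2.
- Same-wave results labelled as associations that do not show explanation.

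Soften the Discussion sentence on explaining inequalities to match. The second hypothesis needs no change.

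The cost is analysis-plan wording, with no new data. The downsides should be named in the plan. Lagged effects are usually smaller and less precise. Adjusting for t1 CASP can remove mediation already present at t1. Measurement error in CASP leaves some false mediation. Unmeasured confounding of factor and outcome remains, as in any observational study.
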